**Fig. 1 Fig1:**
[figure not shown]
Study Flow Diagram

**Table 1 Tab1:** Visual Clotting Score and Heparin Protocol

Clotting Score	Dialyser/Venous Chamber Appearance (at the end of each HD session)	Heparin Dose Adjustment (for the next HD session)
0	Clear	Decrease^a^ boost by 200 units *and* decrease running dose by 200 units/h
1	Few strands/small clot	Decrease^a^ boost by 200 units *and* decrease running dose by 200 units/h
2	½ clotted	Increase boost by 200 units *and* increase running dose by 200 units/h and *maintain* this new heparin dose for the remainder of this study phase only.
3	¾ clotted (able to return blood)	Increase boost by 300 units *and* increase running dose by 300 units/h
4	Completely clotted (unable to return blood)	Increase boost by 400 units *and* increase running dose by 400 units/h

*HD* haemodialysis

NOTE

1) If there is unusually prolonged bleeding from vascular access sites post-HD, for the next HD session, decrease^a^ heparin running dose by 200 units/h and turn heparin off 30 min earlier than usual

2) If there is a discrepancy in score between the dialyser and the venous chamber, the heparin dose adjustment is based on the dialyser clotting score

^a^The minimum possible heparin boost and running dose are 500 units (boost) and 500 units/h. If the heparin dose is to be decreased to less than 500 units (boost and/or running dose) for the next HD session, discontinue the boost and/or the running dose

Randomisation is determined by a computer generated random number list and concealed in sequentially numbered, opaque, sealed envelopes to ensure allocation concealment. Following informed consent and enrolment, the envelope containing allocation sequence is provided to the research coordinator who implements the sequence assignment according to protocol. The intervention and control dialysates, CD and AD, are packaged identically by the manufacturer (Chief Medical Supplies, Ltd., Calgary, Alberta, Canada) for blinding of investigators, patients, and health care staff. All data is confidential, and entered into electronic records by an independent data entry clerk who is blinded to patient allocation.

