### Cumulative heparin dose

The CHD is calculated per HD session, and determined from HD run sheets. Specifically, CHD is the initial heparin bolus, plus the hourly heparin infusion rate multiplied by the time on HD during which heparin is infused, per session, in heparin units. For the primary outcome, the CHD for the last two HD runs of each study phase are recorded, averaged, and used to calculate change from baseline CHD. The last two HD sessions of each phase is chosen to allow adequate time in each phase for heparin dose minimisation.

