## Statistical analysis

Baseline characteristics will be presented as means and 95 % confidence intervals (CIs) or medians and interquartile range (IQR) for continuous variables, and absolute and relative proportions for categorical variables. To determine the effect of CD compared with AD on reduction in CHD (the primary outcome) a random intercept linear mixed model will be used, with CD or AD as the main exposure, subjects as source of random effects, baseline heparin dose values as covariate (at least 2 of 3 measures from the first of two weeks of each period), and final heparin dose values as outcome (at least 2 of 3 measures of the second week of each period). This model takes into account the correlation of data caused by repeated measures for each subject given the crossover design of the study. Treatment, treatment period, and treatment sequence will be modelled as fixed effects. If there is no evidence of period or carry-over effects, all comparisons will be presented relative to AD, without the need for consideration of carry-over effects.

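### The primary outcome is one averaged dose per phase in one section and 2–3 session doses per period in another; a patient-only random intercept fitted to the session doses would understate the standard error

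*Protocol article*

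**What the plan says.** Under Cumulative heparin dose, the article says that "the CHD for the last two HD runs of each study phase are recorded, averaged, and used to calculate change from baseline CHD". That gives one value per patient per phase, taken from sessions 5 and 6 of six.

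Under Statistical analysis, it says "a random intercept linear mixed model will be used, with CD or AD as the main exposure, subjects as source of random effects". The outcome there is "final heparin dose values as outcome (at least 2 of 3 measures of the second week of each period", that is, two or three values drawn from sessions 4 to 6. The covariate is "baseline heparin dose values as covariate (at least 2 of 3 measures from the first of two weeks of each period". The section adds: "Treatment, treatment period, and treatment sequence will be modelled as fixed effects". It justifies the model with: "This model takes into account the correlation of data caused by repeated measures for each subject given the crossover design of the study". It mentions no averaging, and no patient-by-period effect or other within-period covariance.

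Table 1 sets each session's dose by a step up or down from the previous one. After a score of 2 the dose is stepped up once and the nurse maintains "this new heparin dose for the remainder of this study phase only".

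**The concern.** Treatment changes only between a patient's two periods. The error relevant to citrate versus acetate is therefore how much a patient's dose level varies from period to period, not how much it varies between sessions within a period. A patient random intercept captures what all of a patient's doses share. Given the patient, it treats the two or three doses in one period as no more alike than doses from different periods. Under Table 1 they should be more alike, because they are successive steps of one titration and often repeats of one held dose.

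If session rows are fitted this way, repeats of one titrated dose count as extra evidence on treatment. Confidence intervals become too narrow and the false-positive rate exceeds 5% for the primary comparison. Separately, two analysts following the two sections would analyse different sessions and a different number of values per patient.

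**Working it through.** **The plan's own figure.** Inputs from Sample size calculations: SD 900, difference 1000 units, alpha 0.05 (taken as two-sided), power 80%, dropout 30%. For a crossover with one value per period, n = ((1.96 + 0.84) × SD_diff / 1000)², with SD_diff = 900 × √(2(1 − ρ)). The within-patient correlation ρ is not given. With ρ = 0, n = 12.7, so 13, and 13/0.70 = 18.6, so 19, close to the stated 20. With ρ = 0.5 the total is 10. The stated size is thus consistent with one value per period. Twenty enrolled with 30% dropout leaves 14.

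**Set-up.** Let m be the sessions per period (2 or 3), n the number of patients, and w the share of within-patient variance at patient-by-period level. The documents do not give w, so it is varied. Within-patient variance is scaled to 1.

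- True variance of the treatment difference: 2(w + (1 − w)/m)/n.
- Pooled within-patient mean square used by the patient-only model: MS = [(n − 2)(mw + 1 − w) + 2n(m − 1)(1 − w)] / [(n − 2) + 2n(m − 1)].
- Variance the model reports: 2·MS/(mn).
- Approximate type I error: 2Φ(−1.96 × r), where r = model SE / true SE.

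**Worked case, n = 14, m = 2, w = 0.5.** True variance = 2 × 0.75/14 = 0.107. MS = (12 × 1.5 + 28 × 0.5)/(12 + 28) = 32/40 = 0.80. Model variance = 2 × 0.80/28 = 0.057. r = √(0.057/0.107) = 0.73, and type I error = 2Φ(−1.43) = 15%.

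**Results, n = 14.** The simulated columns come from 40,000 null trials per cell with a z test.

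| w | r, m = 2 | type I, formula | type I, simulated | r, m = 3 | type I, formula | type I, simulated |
|---|---|---|---|---|---|---|
| 0.2 | 0.88 | 9% | 9.5% | 0.80 | 12% | 12% |
| 0.5 | 0.73 | 15% | 16% | 0.62 | 23% | 23% |
| 0.8 | 0.62 | 23% | 25% | 0.49 | 34% | 35% |
| 1.0 | 0.55 | 28% | 30% | 0.42 | 41% | 43% |

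At w = 0 the ratio is 1 and there is no fault. With n = 20 the values are almost the same (29% and 41% simulated at w = 1). Using t instead of z in the session-level model lowers the rate by only about 1 point.

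**Same data, one mean per patient per phase, t test:** 5% in every cell.

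**Is w likely to be small?** Running Table 1's rules under the null, with an assumed 4-hour infusion and assumed scoring noise, gave identical last two doses in about 85–88% of phases. Type I error in such runs was 8–29% under one set of assumptions and 24–54% under another. It was still 38–42% with the week-1 covariate and m = 3. These runs show the direction. Their level depends on inputs the documents do not give, and some model fits had convergence warnings.

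**The case against.** The strongest reply is that the fault may not be there at all. The Cumulative heparin dose section says plainly that the primary outcome is averaged. The 2-of-3 wording can then be a completeness rule for a weekly summary. The covariate uses the same wording and no week-1 session is paired with a week-2 session, which fits a summary value. Each patient then contributes two values, a patient intercept is adequate, and the sentence on repeated measures in a crossover is correct. This reading stands as possible. It does not reconcile the sections: one uses exactly the last two sessions, while the other allows any two or all three of the second week, including session 4, and says nothing of averaging.

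A reader might also infer that the model treats all doses as independent. It does not; it allows for correlation among all of a patient's values and omits only the extra part within a period. A reader might take the top of the range as the expected error. That assumes no session-to-session variation within a period, which Table 1 does not guarantee: scores of 0 or 1 keep lowering the dose, scores of 3 or 4 raise it without a hold, and prolonged bleeding changes the rate and the infusion time.

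Finally, the degrees-of-freedom method is commonly left to a full analysis plan, so its absence here is not a finding. It appears below only because the trial is small.

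**Conclusion.** The two sections define the primary outcome differently and must be reconciled. That holds on any reading.

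The consequence for inference is conditional. If the Statistical analysis section is applied literally to session rows, the standard error is about 0.88 to 0.55 of its true value with two sessions and 0.80 to 0.42 with three. Type I error is then about 9–30% and 12–43% for a nominal 5% test. This assumes 14 evaluable patients, w from 0.2 to 1, and balanced sequences. If the last two sessions are averaged first, the error rate is 5% with a t test. The documents therefore do not support the stronger statement that the planned primary test is invalid outright. Nor do they support a change to the sample size, since a one-value-per-period calculation already gives about the stated 20.

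**What to change.** In Statistical analysis, state that the outcome is one value per patient per phase: the mean CHD of the last two sessions, as the Cumulative heparin dose section already defines. Fit it with a patient random intercept, fixed treatment, period and sequence, and small-sample (t-based) inference. If session-level rows are preferred, add a patient-by-period random effect, so that the treatment contrast is judged against period-level variation.

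In either case, replace the wording on at least two of three second-week measures so that both sections name the same sessions. If that wording was meant as a rule for missing sessions, say so separately and state which value is used when one of the last two is missing.

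The cost is wording only. No data collection or sample size changes. Intervals will be wider than a session-level fit without the extra term would give.

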## Discussion

CD has the potential to decrease intradialytic anticoagulation requirements, and improve patient outcomes. However, existing literature comparing CD to AD is limited. Most studies are small, observational in nature, and focus on dialysis adequacy, dialyser reuse/clotting, or metabolic/inflammatory/haemodynamic parameters [17–23, 25, 27]. Only two prospective randomised studies comparing CD to AD have been performed. One single-centre, unblinded crossover study randomised twenty-three maintenance HD patients to first receive CD without anticoagulation or AD with a Tinzaparin bolus [29]. If the CD session revealed early clotting of the venous chamber or dialyser, a Tinzaparin bolus at half the usual dose could be given, and repeated once. During the HD sessions with CD, 50 % of patients did not require anticoagulation, 32 % required a reduced Tinzaparin bolus, and 18 % stopped HD early due to clotting without Tinzaparin. Of those who received anticoagulation with CD, the median dose of Tinzaparin received was 40 % of the standard dose. There was no difference in dialysis adequacy between groups [29]. The main limitation of this study is that the two groups were not treated equally; unlike the CD group, no attempt was made to reduce anticoagulation in the AD group [29]. Another single-centre, single-blinded, crossover study randomised twenty-five clinically stable maintenance HD patients to receive either AD or CD weekly in an alternating fashion for four weeks [28]. The primary outcome was systemic haemodynamics; secondary outcomes were coagulation activation, acid–base balance, calcium balance, and dialysis adequacy. Compared with AD, the CD group had significantly lower blood pressure and peripheral vascular resistance without any difference in stroke volume. However, the decrease in SBP was ablated with dialysate calcium supplementation in the last study week. CD resulted in a significant increase in pre-HD bicarbonate levels, lower post-HD ionized calcium, and higher Kt/V without any effect on coagulation parameters [28]. This study did not assess the effect of CD on intradialytic heparin dose (heparin was used per usual protocol in both groups); the effect of CD on IDH was also not examined [28].

Four observational studies specifically address heparin use with CD in maintenance HD patients [24, 26, 30, 39]. One study included 277 chronic HD patients from eight HD units in an eight-week long, open-label, sequential four-phase study [26]. The primary outcome was change in mean effective conductivity clearance with CD (and reduced heparin) versus AD (and standard heparin dose). Each study phase was two weeks long (6 HD sessions). In the first baseline phase, patients received AD and 100 % of their standard heparin dose. In subsequent phases, patients received CD and decreasing amounts of heparin (second phase: CD and 100 % of standard heparin dose; third phase: CD and 80 % of standard heparin dose; fourth phase: CD and 2/3 of standard heparin dose). At the end of the study, there was no difference in dialysis adequacy between baseline (AD with 100 % heparin) and subsequent phases (CD with decreased heparin). Even with a 33 % reduction in heparin, there was no difference in HD circuit clotting, and dialysis adequacy was maintained [26]. This study did not assess if a reduced heparin dose was possible with AD [26]. In another prospective study, chlorhydric-acid based dialysate was compared with CD in ten patients treated with post-dilution online haemodiafiltration [24]. During treatments with CD, the heparin dose was decreased by half, then completely discontinued. In 120 CD sessions without heparin, dialysis adequacy was unchanged, and only one clotting episode related to vascular access stenosis was experienced [24]. Two further observational studies, published in abstract form only, included 20 and 31 chronic HD patients, respectively, who had prolonged bleeding from vascular access needling sites post HD. Patients were switched from AD to CD, and intradialytic heparin doses were reduced by 30 % [19, 39] after two months, and 55 % [30] after four months, respectively. In both studies, heparin reduction with CD was achieved without decrease in dialysis adequacy [30, 39].

Although existing literature suggests that CD use during chronic HD allows intradialytic heparin reduction without sacrifice of dialysis dose, and without other adverse effects, this has yet to be investigated in a rigorous trial. We have presented in detail the motivation, design and strategy for our randomised controlled trial, including methods of recruitment, randomisation, allocation concealment, dialysis intervention, outcome assessment, and data collection. The study protocol is developed according to Standard Protocol Items: Recommendations for Interventional Trials (SPIRIT) 2013 [40]; results will be reported following the Consolidated Standards of Reporting Trials (CONSORT) statement [41].

In summary, our randomised crossover trial of chronic HD patients will determine if CD decreases intradialytic heparin requirements, and its affect on haemodynamic stability and dialysis adequacy. Our study will answer a clinically relevant and important question which has not previously been addressed by a well-designed randomised trial.

## Abbreviations

HD: Haemodialysis
CD: Citrate dialysate
CHD: Cumulative heparin dose
AD: Acetate dialysate
PT: Prothrombin time
INR: International normalised ratio
aPTT: Activated partial thromboplastin time
B2M: Beta-2-microglobulin
CRP: C-reactive protein
FBV: Fibre bundle volume
IDH: Intradialytic hypotension
SBP: Systolic blood pressure
CIs: Confidence intervals
IQR: Interquartile range
